## PRÉCIS

### Study Title

Use of Behavioral Economics and Social Psychology to Improve Treatment of Acute Respiratory Infections (BEARI): A cluster randomized controlled trial [IRC4AG039115-01]

### Objectives

The main intent of this study is to determine whether interventions that leverage information technology and apply behavioral economic concepts reduce the rate of antibiotic prescribing for ARIs. Our primary hypothesis is that practices randomized to receive behavioral economic interventions will have lower antibiotic prescribing rates for non-antibiotic appropriate ARIs compared to control practices. We further hypothesize that for the treatment conditions, individual prescribers' rates of antibiotic prescribing for encounters with a non-antibiotic appropriate ARI diagnoses will decrease relative to their own historical control rates.

### Design and Outcomes

We will conduct a multi-site cluster randomized trial of 3 behavioral interventions targeting unnecessary antibiotic prescribing during ambulatory visits for acute respiratory infections (ARIs), with practice as the unit of randomization.

The main outcome will be the rate of antibiotic prescribing for ambulatory visits for acute respiratory infections in which antibiotics are inappropriate (i.e., prescribing an antibiotic is inconsistent with published guidelines).

In the main analysis, we will compare a 6-month baseline period to an 18-month intervention period. In subsequent secondary analysis, we will track antibiotic prescribing for another 12 months after the interventions end.

### Interventions and Duration

The intervention period will be 18-months in length for all participants, with a one year follow-up period to measure persistence of effects after interventions end. The following interventions will be compared: *Accountable Justification (AJ)* (also known as "Justification Alerts," or JA) is an EHR-based intervention which will prompt the clinician to justify, in a free text response, the decision to prescribe an antibiotic for each ARI. The prompt is designed to inform the clinician that the justification will be seen by others in the patient's medical record as an "Antibiotic Justification" note, and that if no justification is entered, the phrase "no justification given" will appear in the note. *Suggested Alternatives (SA)* is an EHR-based intervention most closely resembling

traditional clinical decision support alerts and order sets. ARI diagnoses will trigger a pop-up screen that states, “Antibiotics are not generally indicated for [this diagnosis]. Please consider the following prescriptions, treatments, and materials to help your patient.” The screen will then suggest a list of alternatives see Appendix D: Example of Suggested Alternatives order set), each with a streamlined order entry option, such as for over-the-counter and prescription medications (e.g., decongestants) and letter templates excusing patients from work. *Peer Comparison (PC)* is an email-based intervention. Clinicians will be ranked from highest to lowest inappropriate prescribing rate within each region using EHR data. Clinicians with the lowest inappropriate prescribing rates (the top-performing 10th percentile) will be informed that they are a “Top Performer” in a congratulatory email. The remaining clinicians will be told that they are “Not a Top Performer” by email. Emails will include the number and proportion of inappropriate antibiotic prescriptions written for a month for non-antibiotic-appropriate ARI cases and the proportion written by Top Performers.

#### **Sample Size and Population**

We will recruit physicians and advance practice nurses from 49 primary care clinics affiliated with three healthcare organizations who see acute respiratory infection patients. Approximately 300 eligible providers seeing acute respiratory patients will be recruited for this study.

We will randomize practices (blocking on geographical region) to 0, 1, 2, or 3 interventions in a 2x2x2 factorial design to avoid contamination between individual clinicians within the same practice.

## **1. STUDY OBJECTIVES**

### **1.1 Primary Objective**

Our primary hypothesis is that practices randomized to receive behavioral economic interventions will have lower antibiotic prescribing rates for non-antibiotic appropriate ARIs compared to control practices.

### **1.2 Secondary Objectives**

Secondary outcomes will examine antibiotic prescribing more broadly (including ARI diagnoses for which antibiotics might be appropriate), and extend the analysis for another 12 months of follow-up to investigate persistence of effects.

## **2. BACKGROUND AND RATIONALE**

### **2.1 Background on Condition, Disease, or Other Primary Study Focus**

Acute respiratory infections (ARIs) constitute about 10% of all ambulatory care visits in the United States and account for 44% all antibiotic prescriptions provided in ambulatory care. Despite the fact that the vast majority of ARIs in adults are caused by viruses, antibiotic use for ARIs remains common. Although the Centers for Disease Control and Prevention and others have placed increased emphasis on reducing inappropriate antibiotic use, prescribing rates declined only modestly between 1995 and 2006, and the use of broader-spectrum antibiotics increased.

Clinicians who prescribe antibiotics for non-bacterial infections expose patients to unnecessary risks of adverse drug events, and increased costs. Furthermore, antibiotic overuse increases the spread of antibiotic-resistant bacteria which have become a major public health problem. Educational interventions may have limited impact on prescribing rates if lack of guideline awareness is not the primary reason for inappropriate antibiotic prescribing.

Recognizing the limitations of educational and informational interventions, we have developed novel interventions, drawing on insights from behavioral economics and social psychology, designed to appeal to provider self-image and social motivation and thereby produce larger and more enduring effects. These interventions take into account a growing body of research indicating that individuals act within broad social contexts and behave in ways that are not always rational but may be predictable.

### **2.2 Study Rationale**

*Rationale for Accountable Justifications.* In the Accountable Justifications intervention, clinicians will be prompted to record an explicit justification for why they are prescribing an antibiotic to a patient with an ARI that appears in the patient's EHR. Accountable justifications incorporate several behavioral principles. First, they signal an injunctive norm (a norm, often provided by an authoritative source, that strongly indicates how people should behave) indicating that prescribing an antibiotic is not recommended. This may make the provider more likely to believe both that not prescribing an antibiotic is the best medical decision and that prescribing when it is not indicated violates professional standards. Second, they incorporate social accountability. Provider justifications become an explicit, separate part of the medical record, so a provider's decision to prescribe is subject to the review and judgment of the provider's peers. Third, the justification alert implicitly designates guideline-concordant prescribing as the default action. Defaults are options that are exercised if the decision maker takes no special action to opt in or out of a given choice. Prior to our intervention, choosing to deviate from guidelines did not carry a special requirement to document a clinical rationale in the EHR. Accountable justifications, therefore, reset the default action. Guideline-concordant treatment choices (i.e., not prescribing an antibiotic for an ARI) will continue to require no special justification, but a provider must now "opt-in" to prescribing an antibiotic by providing a justification for which they are accountable.

*Rationale for Suggested Alternatives.* When clinicians assigned to the Suggested Alternatives intervention see a patient with an ARI, they will receive a list of non-antibiotic treatment choices prior to the time when they would complete an antibiotic prescription. Suggested Alternatives may be effective because one central reason why physicians prescribe antibiotics for ARIs when they are not indicated is perceived pressure from patients requesting a prescription. Patients may be unsatisfied if they do not receive an antibiotic prescription, or at least a prescription for medication of some kind. By making prescription and over-the-counter medications that are alternatives to antibiotics more salient to providers, we facilitate a means by which they can satisfy patient demand for treatment from their provider while at the same time reducing their tendency to prescribe unnecessary antibiotics.

*Rationale for Peer Comparisons.* Social norms are standards that are understood by members of a group and that guide relevant social behavior due to a desire to conform with actual behavior (the descriptive norm) or sanctioned behavior (the injunctive norm). Numerous studies have shown that people tend to conform to the behavior of others, especially those who are perceived to be similar to one's self. Such effects have been found in studies of behaviors as diverse as voting, littering, and towel recycling in hotels. Social norms may convey information concerning appropriate behavior or social consequences of failing to conform. Behavioral studies find that these effects persist even when behavior is unobservable (e.g., littering when nobody is around) and when the social information is not particularly informative to one's own preferences (e.g., towel recycling). We expect that periodically reminding health care providers of their own prescribing behavior, while providing both a descriptive social norm (displaying the behavior of the best performing peers in their region) and an injunctive norm (citing the national recommended guidelines) will lead providers to conform more closely to these norms. A seminal study by Kiefe et al. demonstrated that providers who were shown their own performance in relation to 90th percentile performance on measures of preventive and chronic disease care had greater performance

improvements than those who were shown their own performance in relation to mean performance. Thus, in the current study those in the Peer Comparison conditions will be provided personalized feedback along with the antibiotic over-prescribing rate of only the top performers within their clinic. In addition, injunctive norms (i.e., indicators of socially desirable performance for high performers) are often excluded. These factors suggest that the use of benchmarks can be improved by applying “nudging” interventions with foundations in social decision making. Our performance feedback reports for each provider randomized to receive the Peer Comparison intervention will have three key characteristics: (1) each target provider will receive his or her individual performance, (2) benchmarks will prominently feature the performance of providers who would be considered credible peers of the target provider, and (3) benchmarks will reflect *only* performance that is desirable (e.g., showing only the performance of the best-performing credible peers).

### **3. STUDY DESIGN**

The Use of Behavioral Economics and Social Psychology to Improve Treatment of Acute Respiratory Infections (BEARI) Trial is a multisite, cluster-randomized controlled trial with practice as the unit of randomization. The primary aim is to test the ability of three interventions based on behavioral economic principles to reduce the rate of inappropriate antibiotic prescribing for ARIs. We will randomize practices in a 2 x 2 x 2 factorial design to receive up to three interventions for non-antibiotic-appropriate diagnoses: 1) Accountable Justifications: When prescribing an antibiotic for an ARI, clinicians are prompted to record an explicit justification that appears in the patient electronic health record ; 2) Suggested Alternatives: Through computerized clinical decision support, clinicians prescribing an antibiotic for an ARI receive a list of non-antibiotic treatment choices (including prescription options) prior to completing the antibiotic prescription; and 3) Peer Comparison: Each provider’s rate of inappropriate antibiotic prescribing relative to top-performing peers will be reported back to the provider periodically by email. We will enroll approximately 300 clinicians (practicing attending physicians or advanced practice nurses) from 49 participating outpatient clinic sites and collect baseline data. All participating clinicians will receive a brief educational module reviewing ARI treatment guidelines at the time of consent and enrollment. Surveys will be administered at the time of enrollment and after the intervention is complete. The primary outcome is the antibiotic prescribing rate for office visits with non-antibiotic-appropriate ARI diagnoses. Secondary outcomes will examine antibiotic prescribing more broadly. The 18- month intervention period will be followed by a one year follow-up period to measure persistence of effects after interventions cease. Data from electronic medical records for participating practices are transferred to the Data Coordinating Center on a weekly basis.

## **4. SELECTION AND ENROLLMENT OF PARTICIPANTS**

### **4.1 Inclusion Criteria**

The subjects involved in this trial are clinicians who will be recruited from multiple clinical sites in Boston and Los Angeles. The target group of physicians (and the patients that they treat) is fully inclusive and representative. Clinicians will be eligible if they treat adult patients with acute respiratory infections. All consenting clinicians at these practices will be offered enrollment.

Each study clinic is required to have an electronic health record (EHR) system in place and have its own physical building (as opposed to multiple clinics sharing the same space, such as the floor of a hospital, where interactions between providers assigned to different intervention groups would be more likely). Clinicians must meet the following inclusion criteria to participate in this study: 1) treat adult patients with acute respiratory infections and practice at one of the study clinics.

An office visit is eligible for inclusion in the outcome denominator if: 1) the patient was 18 years old or older, 2) the provider and practice site were enrolled in the study, and 3) the visit occurred during the 18-month intervention period.

### **4.2 Exclusion Criteria**

Visits will be excluded from the primary analysis when: 1) patients have certain medical co-morbidities that make ARI guidelines less likely to apply, 2) patients have concomitant visit diagnoses indicating a non-ARI possible bacterial infection, 3) patients have concomitant visit diagnoses indicating potentially antibiotic appropriate ARI diagnoses or other ARI diagnoses suggestive of a bacterial infection or 4) the visit occurred within 30 days of an earlier ARI diagnosis. Visits for which a provider records another condition that is not an ARI for which antibiotics might be indicated will also be excluded from the analysis. The sets of diagnoses which will be used to calculate the outcomes are listed in Appendix E: Code Set Definitions.

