### **7.1 Specification of Safety Parameters**

Data elements from qualifying ARI visits for providers enrolled in the study will be collected from the electronic health record. At Partners Healthcare, total qualifying visits will be based on qualifying ICD-9 codes (See Appendix E: Code Set Definitions), while Los Angeles sites also incorporate exclusions of suppressor codes used in the decision to trigger the clinical decision support. Aggregate counts of total ARI visits across sites for which the intervention was triggered, including those for which an antibiotic was not prescribed, and the number of return visits occurring within 30 days of index visits (and associated rate of return) with a diagnosis of concern (See Appendix E for diagnoses of concern at revisit) will be calculated. Of return visits identified with a diagnosis of concern, a random sample of 20% of cases will be generated for chart review by site physicians to determine the possibility of study interventions interfering with proper diagnosis and treatment of a patient. Cases will be examined to determine whether earlier antibiotics would have improved the outcomes and classified as one of the following: earlier antibiotics UNLIKELY to have improved the course, early antibiotics MAY HAVE improved the course, UNCERTAIN if earlier antibiotics would have improved the course.

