#### 9.4.2 Secondary outcomes

To study safety and diagnostic drift we will evaluate an expanded list of potentially appropriate and other diagnoses of interest. For potentially antibiotic appropriate acute respiratory infection diagnoses these are: Acute sinusitis; Acute sinusitis/rhinosinusitis; Acute pharyngitis; 462 Acute pharyngitis. For other acute respiratory infection diagnoses or symptoms of interest these are: Streptococcal sore throat; 034.0 Acute pharyngitis; Cough; and 786.2 Acute bronchitis.

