### 9.5 Data Analyses

We will use the following descriptive statistics to characterize the sample: Means and medians for continuous measures, frequencies for count data, standard deviations and interquartile ranges for variance.

For inferential analysis of our hypotheses, we will employ a mixed-effects hierarchical logistic regression model to estimate the adjusted marginal effect over time of each intervention on the primary outcome using. Fixed effects will include intervention assignment, time period dummy variables (the baseline prescribing rate for each clinician, the intervention and intervention months 0-6, 7-12, and 13-18), and time period interacted with intervention assignment. Providers and randomization unit (clinic) will be included as random effects. To isolate the effect of each individual intervention (Suggested Alternatives, Accountable Justification, or Peer Comparison) on the primary outcome, controlling for any co-occurring interventions under the factorial design.

To assess diagnostic drift, we will use the same analytic model as for the primary outcome, but with the percentage of *all* ARIs that is coded as antibiotic-appropriate in each study arm as the dependent variable (a secondary outcome).

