**You have completed the exit survey. Thank you very much for your participation!**

## APPENDIX C: DETAILS OF DEVELOPMENT AND CUSTOMIZATION THAT WAS REQUIRED AT EACH SITE

| Requirement/Feature                                                                                                        | Longitudinal Medical Record                                                                         | NextGen                                                                                            | EpicCare                                                                                                                 |
|----------------------------------------------------------------------------------------------------------------------------|-----------------------------------------------------------------------------------------------------|----------------------------------------------------------------------------------------------------|--------------------------------------------------------------------------------------------------------------------------|
| Application of eMeasure exclusion criteria from problem list, past diagnoses, and concomitant diagnoses to suppress alerts | Not Implemented                                                                                     | Typical customization of existing functionality                                                    | Typical customization of existing functionality                                                                          |
| Justification Text Inserted into a visible portion of the medical record                                                   | Expert programming                                                                                  | Expert programming                                                                                 | Expert programming                                                                                                       |
| Default text “No justification Provided” populating medical record                                                         | Expert programming                                                                                  | Expert programming                                                                                 | Expert programming                                                                                                       |

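### A same-visit code for a non-ARI bacterial infection removes a visit from the primary outcome, and neither drift measure is built to count that exit

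*Protocol*

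**What the plan says.** Protocol Section 4.2 lists the exclusions from the primary analysis, and Section 9.1 (Outcome measures) repeats them. Three depend on what the clinician codes at the visit itself:

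- a visit leaves when "patients have concomitant visit diagnoses indicating a non-ARI possible bacterial infection";
- it leaves when "patients have concomitant visit diagnoses indicating potentially antibiotic appropriate ARI diagnoses or other ARI diagnoses suggestive of a bacterial infection";
- and "Visits for which a provider records another condition that is not an ARI for which antibiotics might be indicated will also be excluded".

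Section 5.3 foresees that providers may change diagnoses to avoid alerts or poor performance reports. Its audit compares likely bacterial with likely viral ARIs, clinician by clinician. Section 9.4.2 states: "To study safety and diagnostic drift we will evaluate an expanded list of potentially appropriate and other diagnoses of interest". Section 9.5 then defines the drift outcome: it takes the percentage of all ARIs "that is coded as antibiotic-appropriate in each study arm as the dependent variable".

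Appendix C has a row headed "Application of eMeasure exclusion criteria from problem list, past diagnoses, and concomitant diagnoses to suppress alerts". It is marked as not implemented for the Longitudinal Medical Record and as customised for NextGen and EpicCare. Section 7.1, on safety counts, is consistent with this. It contrasts Partners Healthcare, which uses qualifying codes, with Los Angeles: "Los Angeles sites also incorporate exclusions of suppressor codes used in the decision to trigger the clinical decision support".

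**The concern.** The exclusion depends on something that happens after randomisation, under the control of a clinician who knows the assignment (the module in Section 4.3 describes it). If an intervention leads clinicians to add a non-ARI bacterial code to visits where they prescribe, those visits leave the denominator. The observed rate then falls although prescribing has not changed.

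All three interventions give some reason to do this. Peer Comparison scores the same diagnoses as the primary outcome (Table 1), and at NextGen and EpicCare sites a concomitant diagnosis can also suppress the prompt. The protocol recognises the risk and fixes a check for it, but that check looks only at movement among ARI codes. A lower rate produced by this route could therefore sit beside a reassuring drift result.

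**Working it through.** **Which exits the checks can see**

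| Exit from the primary denominator | Audit, Section 5.3 | Drift outcome, Section 9.5 |
|---|---|---|
| Antibiotic-appropriate ARI code added | Counted if classed as likely bacterial | Rises directly |
| Non-ARI bacterial code added | Not counted | Unchanged if the visit stays among all ARIs; small rise if it drops out |
| Coded only as cough (786.2) | Classification not stated | Numerator not raised, but cough is on the Section 9.4.2 list |

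**Inputs.** Section 9.2 gives a baseline rate p = 0.50, a target difference d = 0.07 and 16 visits per provider. Assumed:

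- f, the excess share of antibiotic visits recoded;
- q, the share of removed visits that had an antibiotic (1 unless stated);
- b, the share of all ARIs coded antibiotic-appropriate (20% to 40%).

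The plan has no recoding figure to reproduce. Its provider arithmetic agrees: 376 × 0.75 = 282; 282 / 2 = 141; 2,252 / 141 = 16.0. The 2,252 visits could not be reproduced from the stated inputs, because no cluster size is given. Nothing below depends on it.

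**Apparent fall with no change in prescribing.** Observed rate = p(1 − f) / (1 − pf).

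| f | Observed rate | Apparent fall |
|---|---|---|
| 5% | 0.475 / 0.975 = 48.7% | 1.3 points |
| 10% | 0.450 / 0.950 = 47.4% | 2.6 points |
| 15% | 0.425 / 0.925 = 45.9% | 4.1 points |
| 20% | 0.400 / 0.900 = 44.4% | 5.6 points |

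The share of all eligible visits needed to mimic d is r = d / (1 − p + d) = 0.07 / 0.57 = 12.3%. That is 0.123 / 0.50 = 24.6% of antibiotic visits, or about 2 of 16 per provider.

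**Sensitivity.**

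- If only 80% of the removed visits had an antibiotic, removing 5% of all visits gives (0.50 − 0.05 × 0.80) / 0.95 = 48.4%. The fall is 1.6 points instead of 2.6. Reaching 7 points then needs 0.07 / (0.80 − 0.43) = 18.9% of all visits.
- At baselines of 30%, 40% and 60%, a 7-point fall needs 30%, 26% and 25% of antibiotic visits.
- Only the excess over control counts. If control clinics recode 5% (48.7%) and intervention clinics 15% (45.9%), the spurious difference is 2.8 points.

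**Response of the drift outcome at f = 10%** (r = 5% of visits outside the antibiotic-appropriate group).

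- Non-ARI code added, visit still counted as an ARI: change 0.
- Non-ARI code added, visit leaves the ARI denominator: b / (1 − (1 − b)r) gives 0.20 / 0.96 = 20.8% and 0.40 / 0.97 = 41.2%, a rise of 0.8 to 1.2 points.
- The same visits given an antibiotic-appropriate ARI code instead: b + (1 − b)r gives 24% and 43%, a rise of 3 to 4 points.

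At r = 12.3% the three results are 0, about 2 to 3 points, and about 7 to 10 points. The drift outcome therefore responds to the ARI route and hardly or not at all to the non-ARI route.

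**Effect of keeping the visits.** If the recoded visits stay in the denominator, the rate returns to 50% and the spurious difference to 0.

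**The case against.** Several parts of the case against stand.

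- **Not all same-visit coding is hidden.** An added antibiotic-appropriate ARI code is what the drift outcome is designed to detect, and the figures above show that it would.
- **One code does not avoid both prompt and score everywhere.** Suppression is documented only for NextGen and EpicCare. Where it is not implemented, the code affects the outcome but not the alert. If recoding occurred only at Los Angeles sites holding an assumed 30% to 60% of visits, mimicking 7 points would need 82% to 41% of their antibiotic visits.
- **Cough is not ignored.** Table 1 lists it as triggering decision support, and Section 9.4.2 puts it among the diagnoses examined for drift. What remains is that the percentage in Section 9.5 has no numerator term for it.

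Other points stand only in part.

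- Section 1.2 promises a broader prescribing outcome, and Table 1 marks further diagnoses for secondary assessment. But Section 9.5 describes a model only for the primary and drift outcomes. Nothing says the broader outcome retains visits with a non-ARI bacterial code, and the Appendix E code sets are in a separate file.
- The dashboards in Section 10.3.2 review coding before each email, but are not said to compare exclusions by arm.
- The difference-in-differences model removes stable coding habits and common trends. It does not remove recoding that starts with the intervention, which falls on the interaction of assignment and time.
- Supportive analyses often belong in the SAP, which is not at hand. Here, however, the protocol itself fixes both the exclusion and a drift measure that misses it.

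A reader might also infer that the 30-day rule ("the visit occurred within 30 days of an earlier ARI diagnosis") works the same way by hiding deferred antibiotics. It depends on an earlier visit, not on same-visit coding, and applies in every arm. The documents do not show in which direction it would act.

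**Conclusion.** The point holds for one specific route. A same-visit code for a non-ARI possible bacterial infection removes a visit from the primary denominator, and both stated drift measures are blind or nearly blind to it. Excess recoding in intervention clinics would bias the primary comparison towards benefit by about 2.6 points at 10% of antibiotic visits and 5.6 points at 20%. This assumes a 50% baseline, unchanged prescribing and an antibiotic at every removed visit; the bias is smaller if some removed visits had none.

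A reader might infer that recoding could plausibly account for the whole 7-point target. The documents do not support that. The figure is reached only by solving backwards to about 25% excess recoding, and the protocol gives no recoding rate. The finding is that the plan as written could not detect or bound this bias, not that the bias will occur. Which codes qualify cannot be checked without the Appendix E file.

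**What to change.** In Sections 9.4.2 and 9.5:

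1. Keep the existing drift outcome and add a second one with the same mixed model: whether a visit carrying a primary-set ARI code is excluded because of a same-visit diagnosis. Report it by route (non-ARI bacterial code; antibiotic-appropriate or other ARI code), by arm and by period, with the share of ARI visits coded only as cough.
2. Add a supportive analysis of the primary hypothesis, with the same model, that retains visits excluded only by same-visit diagnoses. Report it beside the primary result. The comorbidity and 30-day exclusions stay as they are.

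The cost is wording and a few extra model runs on ARI visits that Section 10.2 already has the sites extract. The drawback is that the supportive denominator includes some visits with genuine bacterial infections and so dilutes the effect. It supports the primary analysis and does not replace it.
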